
### Primary and Secondary Endpoints

This study’s primary outcome is the quantification of improvement in cognitive and motor performance from baseline to 12 months after VPS surgery or ETV. Secondary outcomes include the rate of postoperative complications (e.g., infection, device malfunction, or over-drainage), length of hospitalization, ICU stay, and patient-reported quality of life. To ensure that the study has sufficient power to detect meaningful differences between the two surgical groups, a power analysis was conducted. This analysis determined that a total sample size of 100 patients (50 in each group) would be required to achieve a power of 80% to detect an effect size (d) of 0.5 at a significance level of 0.05. The randomized controlled trial design, combined with standardized surgical protocols and the use of advanced neuroimaging and neurostimulation techniques, ensures that the results will be both statistically robust and clinically relevant.

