
### 2.1. Preoperative Evaluation

Preoperative evaluation is critical for establishing a detailed baseline of each patient’s neurological, cognitive, motor, and personality functions. It combines clinical assessments, advanced neuroimaging, and specialized tests to confirm the diagnosis and plan the surgical approach (Figure 1). All neuropsychological assessments, including WAIS-IV, RBMT-3, Raven’s matrices, and MMPI-2, will be administered preoperatively and repeated at each follow-up to allow longitudinal comparison. Motor assessments, including the Timed Up and Go (TUG) Test, Baiobit wearable sensor gait analysis, and the iNPH grading scale, will also be conducted both preoperatively and at each postoperative timepoint.

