### 2.2. Neurological Examination and Scoring Systems

A detailed neurological examination will assess motor, cognitive, and sensory functions, with a particular focus on hallmark symptoms of iNPH, such as gait disturbances and reflex abnormalities. Objective tools include the following:Motor test: Timed Up and Go (TUG) Test, 6 min walk through the Baiobit system, a wearable inertial measurement unit (IMU) to measure precise balance, mobility, and fall risk [4].iNPH grading scale (iNPHGS): a validated tool to quantify the severity of gait, cognitive, and urinary symptoms, ranging from 0 (no symptoms) to 4 (severe impairment) [11].Kiefer score: integrates functional symptom severity with radiological findings, including ventricular enlargement and disproportionate subarachnoid spaces measured using the Evans index [12].

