### 2.3. Neuropsychological Assessment

A series of standardized neuropsychological tests will evaluate the cognitive domains commonly affected in iNPH, providing critical data on intellectual, memory, and personality functioning:Raven’s progressive matrices to measure non-verbal intelligence and assess fluid reasoning and problem-solving abilities independent of cultural or educational background 4.Rivermead Behavioural Memory Test—Third Edition (RBMT-3), a memory test with ecological validity designed to predict memory deficits in real-life scenarios and monitor changes over time [12].WAIS-IV (Wechsler Adult Intelligence Scale—Fourth Edition) to provide a comprehensive evaluation of cognitive abilities, including general intellectual functioning, working memory, fluid intelligence, and processing speed [4,12].Minnesota Multiphasic Personality Inventory—2 (MMPI-2) to assess personality traits and emotional disorders, offering insights into psychological factors that may influence postoperative recovery [11].

In addition to these instruments, the Mini-Mental State Examination (MMSE) will be used to provide a rapid, global assessment of cognitive function. To evaluate balance and fall risk, the Berg Balance Scale (BBS) will be administered, and the Modified Rankin Scale (mRS) will be employed to assess overall functional independence and the degree of disability.

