### 2.11. Statistical Analysis

All statistical analyses will be conducted using IBM SPSS Statistics, version 30.0.0, and R, version 4.5.0. The threshold for statistical significance will be set at α = 0.05. Two-tailed tests will be used unless a specific directional hypothesis is stated (e.g., the anticipated superiority of ETV over VPS), in which case one-tailed tests will be applied.

Continuous variables will first be tested for normality using the Kolmogorov–Smirnov test, and for homogeneity of variance using Levene’s test. If assumptions of normality and homoscedasticity are met, parametric tests such as the independent-samples *t*-test will be used. For repeated measures data, linear mixed-effects models will be applied instead of a traditional ANOVA to account for intra-subject variability and missing data points. If assumptions are violated, appropriate non-parametric alternatives (e.g., Mann–Whitney U test, Wilcoxon signed-rank test) will be applied.

To control Type I errors in multiple comparisons, a Bonferroni correction will be applied where appropriate. In addition to *p*-values, effect sizes (e.g., Cohen’s d for *t*-tests, η^2^ or partial η^2^ for ANOVA) will be reported to quantify the magnitude of observed effects.

For the analysis of longitudinal data, mixed-effects models will be used to account for intra-subject variability across follow-up points. These models will include fixed effects for time and the treatment group, as well as random intercepts to capture individual-level variability.

An a priori power analysis was performed assuming an effect size of Cohen’s d = 0.5, power (1 − β) of 0.80, and α = 0.05 (two-tailed). The estimated required sample size was 51 participants per group. This effect size was selected as a conservative estimate based on previously published studies evaluating pre- and postoperative cognitive and motor changes in patients with iNPH. Nonetheless, we recognize that this estimate may be optimistic. If the true effect is smaller, a larger sample size would be needed to retain adequate statistical power. This limitation is acknowledged, and future extensions of the study may involve adaptive or sequential design strategies to account for observed variability.

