The primary outcome will be the change in cognitive and motor performance over time. Cognitive functions will be evaluated using neuropsychological tests, focusing on memory, attention, executive function, and language. All cognitive assessments will be conducted both preoperatively and at each postoperative follow-up interval, as stated in the protocol. Motor outcomes will be assessed through gait analysis and coordination tests. All motor assessments will likewise be performed preoperatively and postoperatively using standardized tools including the Timed Up and Go (TUG) Test, the Baiobit wearable system, and the iNPH grading scale. The preliminary expectations are that patients in both the ETV and VPS groups will experience significant improvements in gait, as gait disturbance is typically the first symptom to improve following iNPH surgery. However, the degree of cognitive improvement may differ between the two groups, as prior evidence suggests that early intervention and reduced white matter compression may promote better cognitive recovery. By comparing cognitive trajectories in the ETV and VPS groups, this study aims to determine whether ETV has comparable or superior cognitive benefits relative to VPS. Structural changes in the brain will be analyzed using diffusion tensor imaging (DTI) and magnetic resonance imaging (MRI) with flowmetry. DTI will track changes in white matter integrity over the 12-month follow-up period. Since periventricular white matter is particularly vulnerable in iNPH, changes in the integrity of white matter tracts, such as the corticospinal tract, will be examined. The integrity of these tracts is essential for motor coordination and cognitive functions. Tractography will be used to visualize white matter pathways before and after surgery, providing insight into how ETV and VPS differentially affect white matter recovery. Neurophysiological changes will be measured using navigated transcranial magnetic stimulation (nTMS). This technique will allow researchers to assess motor cortical excitability and map changes in corticospinal tract connectivity. Motor evoked potentials (MEPs) will be recorded before surgery and at all follow-up intervals. An increase in MEP amplitude after surgery would suggest improved cortical excitability and the potential recovery of motor function. Differences in MEP amplitudes between the ETV and VPS groups may offer additional evidence regarding which procedure promotes superior motor recovery. Secondary outcomes will include the rate of complications, intensive care unit (ICU) stay, and patient-reported quality of life. Patients in the VPS group are expected to have a higher incidence of device-related complications, such as infection, shunt malfunction, and over-drainage, compared to the ETV group, which does not require the implantation of a foreign device. ICU stay and hospital length of stay will be compared between the two groups, with the hypothesis that ETV patients will have shorter stays due to the less invasive nature of the procedure. Quality-of-life measures will be obtained from patient self-reports, providing insight into the broader impact of surgery on daily living and well-being.

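### The primary outcome spans two domains with no score, success rule or multiplicity family fixed, and the stated 80% power is for one unadjusted comparison tied to no instrument

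*Protocol article*

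**What the plan says.** The section Primary and Secondary Endpoints states that the "primary outcome is the quantification of improvement in cognitive and motor performance from baseline to 12 months". Section 3 (Expected Results) puts it as "The primary outcome will be the change in cognitive and motor performance over time". Neither names a score, a composite or a rule for combining the domains.

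The candidate instruments are spread over Section 2:

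- Cognitive side, Section 2.1: "All neuropsychological assessments, including WAIS-IV, RBMT-3, Raven’s matrices, and MMPI-2, will be administered preoperatively and repeated at each follow-up". Section 2.3 adds the MMSE.
- Motor side, Section 2.1: "Motor assessments, including the Timed Up and Go (TUG) Test, Baiobit wearable sensor gait analysis, and the iNPH grading scale". Section 2.3 adds the Berg Balance Scale.
- Section 2.2 describes the iNPH grading scale (iNPHGS) as "a validated tool to quantify the severity of gait, cognitive, and urinary symptoms".
- Section 2.3 gives the MMPI-2 the task "to assess personality traits and emotional disorders".

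On multiplicity, Section 2.11 says that "a Bonferroni correction will be applied where appropriate". It gives no number of tests and no family.

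On sample size, Section 2.11 assumes d = 0.5, power 0.80 and two-tailed α = 0.05, and arrives at 51 per group. The endpoints section gives 50 per group for the same assumptions. The effect size is attached to no instrument.

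**The concern.** A power statement belongs to a defined test of a defined endpoint. Here the primary outcome covers two domains and several instruments, while the calculation covers one comparison at the full α. Three questions stay open: which scores count, whether one or both domains must be positive, and which tests share the 5%. The answers decide the error rate and the power, and the plan allows them to be settled after the data are known.

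If any favourable score may carry the trial, the false-positive rate exceeds 5%. If α is split or both domains are required, the power falls below the figure stated. The Conclusions section expects the trial to influence guidelines, so this matters.

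There is also a problem of content. A gain on the iNPHGS total could be reported as motor benefit although it came from the cognitive or urinary component.

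**Working it through.** **Inputs.** d = 0.5, α = 0.05 two-tailed and target power 0.80 (Section 2.11); 50 per group (endpoints section) or 51 (Section 2.11). The number of primary tests k is not in the article. I take k = 2 (one score per domain) as the smallest reading. For illustration I also take k = 7 (the instruments named in Section 2.1) and k = 8 (Raven, RBMT-3, WAIS-IV, MMSE; TUG, Baiobit, iNPHGS, Berg). Correlations between test statistics are assumed, from 0 to 0.7.

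**1. The plan's own figure.** Two-sample t-test, d = 0.5:

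- two-sided 0.05, 80% power: 64 per group (63 by normal approximation, 2(1.960 + 0.842)²/0.25);
- one-sided 0.05, 80% power: 51 per group (50 by normal approximation);
- two-sided power: 70% with 50 per group, 71% with 51.

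The stated 50–51 therefore matches a one-sided test, while the text says two-tailed. That is a separate error, but it sets the starting point here at 70%, not 80%.

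**2. Alpha split, power per endpoint.** t-test, 50 per group, each test at two-sided 0.05/k:

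| k | α per test | power per endpoint | n per group for 80% |
|---|---|---|---|
| 1 | 0.05 | 70% | 64 |
| 2 | 0.025 | 59% | 78 |
| 7 | 0.0071 | 41% | 102 |
| 8 | 0.00625 | 39% | 105 |

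For k = 2 the fall from 80% to 59% is 21 points: about 10 from the sidedness error (80 to 70) and about 11 from splitting α (70 to 59). Even on the one-sided basis that reproduces the stated sample size, splitting over two endpoints gives 70%.

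**3. Both domains required, each at 0.05.** Independent: 0.697² = 49%. With correlation (bivariate normal, mean 0.5·√25 = 2.5 for each statistic, critical value 1.960): 54% at 0.3, 56% at 0.5, 60% at 0.7. Under independence, 80% needs about 84 per group.

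**4. Either domain sufficient, no correction.** Independent: 1 − 0.95² = 9.8%. At correlation 0.3, 0.5 and 0.7: 9.4%, 9.0%, 8.4%. For k = 7: 1 − 0.95⁷ = 30% if independent, down to 18% at correlation 0.7. For k = 8: 34% down to 19%.

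**5. Versions that hold up.**

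- One composite, the mean of two standardised scores each with d = 0.5, tested once at 0.05. Its effect size is 0.5/√((1 + ρ)/2), which gives power of 94%, 87%, 82% and 77% at ρ = 0, 0.3, 0.5 and 0.7, with α at 5%.
- Bonferroni over two domains, either sufficient. If independent, power for at least one success is 1 − (1 − 0.590)² = 83%. By the bivariate normal (mean 2.5, critical value 2.241) it is 80%, 76% and 72% at correlation 0.3, 0.5 and 0.7. Family-wise error is at most 5%.

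**6. Baseline adjustment.** If d is on the raw outcome scale and the baseline correlation is 0.5 (assumed; none is stated), the standardised effect is 0.5/√(1 − 0.25) = 0.577, so the expected statistic is 0.577·√25 = 2.887. By normal approximation, power for one test at 0.05 is Φ(2.887 − 1.960) = 82%, and at 0.025 it is Φ(2.887 − 2.241) = 74%.

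**The case against.** The strongest reply is that step 5 shows legitimate versions of a cognitive-and-motor primary outcome with power near 80% at 0.05. This stands. A reader might infer that no version could have the stated operating characteristics, and the documents do not support that. The defect is that the article does not say which version applies.

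A reader might also infer that all seven or eight instruments are primary, with an error rate around a third. The article nowhere says so. The count is an assumption, and 34% needs eight independent tests with any one sufficient. Nor may that error rate be paired with 39% power: the first assumes any single success wins, the second is power for one given test.

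Nor is multiplicity ignored, since Bonferroni is mentioned. The fault is that it has no family and plays no part in the sample size.

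An article may leave detail to a fuller protocol or analysis plan. That would excuse an unnamed subscale. It does not excuse a definite power figure that fails for one two-tailed test and takes no account of the second domain.

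On content, Section 3 describes the cognitive work as "focusing on memory, attention, executive function, and language" and mentions coordination tests, and Section 2 describes no test specifically for language or coordination. The tool lists are introduced as open, so these are minor drafting matters. The same goes for the MMPI-2: its role in Section 2.3 concerns factors affecting recovery, and the domains in Section 3 do not include personality. The iNPHGS listing is firmer, because Section 2.1 and Section 2.2 disagree about what it measures.

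**Conclusion.** The concern holds in this form: score, success rule and multiplicity family are undefined for a two-domain primary outcome, and the stated 80% power belongs to one unadjusted comparison tied to no instrument. With 50 per group and d = 0.5 on each endpoint, two-sided:

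- one test has 70% power, which is the separate sidedness error;
- two endpoints have 59% each at 0.025, or about 49–60% if both must succeed at 0.05;
- either of two sufficient without correction carries a family-wise error of about 8–10%, and seven or eight instruments would carry about 18–34%.

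These figures rest on the assumed number of tests, correlations of 0 to 0.7, an equal effect on every endpoint, no dropout and no gain from baseline adjustment. The conclusion does not rest on a large number of tests: two is enough. It stops short of saying that 80% at 0.05 is out of reach for every choice of primary outcome.

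**What to change.** Before outcome data are seen:

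1. Name one cognitive and one motor score at 12 months as the only primary endpoints, from tools already collected. RBMT-3 total and TUG time are examples; other choices are defensible.
2. State whether one or both must succeed.
3. If either suffices, test at two-sided 0.025 each or by Holm. If both must succeed, say so and test each at 0.05.
4. Restate power for that rule. With 50 per group it is 59% per endpoint at 0.025, before any gain from baseline adjustment. Under independence Holm raises this to 0.590 + (0.697 − 0.590) × 0.590 = 65%. If both must succeed at 0.05, quote about 49–60%. Any baseline correlation used to claim more should be stated and justified.
5. Make all other scores, including the MMPI-2, secondary or exploratory.
6. Do not use the iNPHGS total as a motor endpoint. Section 2.2 gives only a 0 to 4 range and describes no separately scored gait item, so any use of a component would have to be defined first.
7. Align the domains in Section 3 with the tests in Sections 2.2 and 2.3.

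This is a change of wording with no new data collection. The cost is that the other instruments lose primary status and the honest power figure is lower. Keeping 80% at 0.025 per endpoint without baseline adjustment would take 78 per group instead of 50.

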## 3. Expected Results

The results of this study will offer valuable insights into the comparative effectiveness of ETV and VPS in treating patients with iNPH. Cognitive, motor, and structural changes will be analyzed at the preoperative baseline and at 1 week, 3 months, 6 months, and 12 months post-surgery. Data will be collected from 100 patients who will be randomly assigned to either the ETV or VPS group. The analysis will focus on how each surgical approach influences cognitive recovery, gait improvements, and white matter integrity.

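### The 80% power claimed for exactly 50 randomised per group leaves no room for missing 12-month data, and two-tailed power is only about 70% even with complete data

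*Protocol article*

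**What the plan says.** Section 2.11 (Statistical Analysis) takes d = 0.5, power 0.80 "and α = 0.05 (two-tailed") and reports: "The estimated required sample size was 51 participants per group". The Primary and Secondary Endpoints section describes the power analysis as having determined that "a total sample size of 100 patients (50 in each group) would be required to achieve a power of 80" per cent, "to detect an effect size (d) of 0.5 at a significance level of 0.05". The Discussion (section 4) repeats d = 0.5, alpha 0.05 and 80% power for 50 per group and calls that sample sufficiently powered.

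Enrolment is set at 100 patients, 1:1, in the Abstract and section 2. Section 3 adds: "Data will be collected from 100 patients who will be randomly assigned to either the ETV or VPS group". The primary outcome is change from baseline to 12 months, with visits at 1 week and at 3, 6 and 12 months (section 2.10).

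Section 2.11 prefers linear mixed-effects models to ANOVA "to account for intra-subject variability and missing data points". No attrition rate or inflation of the sample size appears. The only caveat on power, in section 2.11 and the Discussion, is that the true effect may be smaller than assumed.

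**The concern.** The number said to be required equals the number to be randomised, so the printed 80% holds only if nobody dies, withdraws or becomes untestable before 12 months. The patients are 60 or older, undergo cranial surgery, and face four follow-ups with neuropsychological testing, MRI with DTI, and nTMS. The analysis section itself allows for gaps in the data. The two accounts of the power analysis also disagree (51 against 50 per group).

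The power figure matters for reading a null result. The Discussion and Conclusions would count a comparable or non-inferior result in favour of ETV. A reader who believes the trial had 80% power will take a non-significant difference as stronger evidence of similarity than it is.

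**Working it through.** **Inputs.** From the article: d = 0.5 (SD = 1 on the standardised scale), alpha 0.05, target power 80%, two-tailed (section 2.11), 1:1 allocation, 50 randomised per group. Assumed, because the article gives no rate: 5, 10, 15 or 20% without a 12-month result, equal in both arms.

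**Step 1: reproduce the printed requirement.** Normal approximation: n per group = 2(z_alpha + z_beta)² / d².

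- Two-sided: 2(1.960 + 0.842)² / 0.25 = 62.8, so 63. The non-central t gives 63.8, so 64.
- One-sided: 2(1.645 + 0.842)² / 0.25 = 49.5, so 50. The non-central t gives 50.15, so 51.

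Neither printed number follows from the stated two-tailed inputs. Both follow from a one-sided 0.05 calculation with no loss: 50 by the normal approximation, 51 by the t-test.

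**Step 2: power at the planned enrolment with complete data** (two-sample t-test, non-central t).

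| n per group | two-sided | one-sided |
|---|---|---|
| 50 | 69.7% | 79.9% |
| 51 | 70.6% | 80.6% |
| 64 | 80.1% | 87.9% |

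The 51-against-50 difference is worth less than 1 point. The sidedness is worth 79.9 − 69.7 = 10.2 points, before any loss.

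**Step 3: add attrition.** Evaluable n per group = 50 × (1 − loss); complete-case t-test at 12 months.

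| Assumed loss | n per group | two-sided | drop | one-sided | drop |
|---|---|---|---|---|---|
| 0% | 50 | 69.7% | – | 79.9% | – |
| 5% | 47.5 | 67.4% | 2.3 | 78.1% | 1.8 |
| 10% | 45 | 65.0% | 4.7 | 76.1% | 3.8 |
| 15% | 42.5 | 62.5% | 7.2 | 73.9% | 6.0 |
| 20% | 40 | 59.8% | 9.9 | 71.6% | 8.3 |

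(Drops in percentage points, from unrounded powers.)

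**Step 4: what the mixed model could recover.** Take a favourable case: every patient lost at 12 months has a 6-month visit, data are missing at random, and the 6-to-12-month correlation r is 0.6 to 0.8 (all assumptions). With m observed at 12 months out of 50, effective n = 1 / [(1 − r²)/m + r²/50].

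- 20% loss (m = 40): r = 0.6 gives 1/(0.64/40 + 0.36/50) = 43.1; r = 0.8 gives 1/(0.36/40 + 0.64/50) = 45.9. Two-sided power is 63 to 66%, against 59.8% complete-case.
- 10% loss (m = 45): effective n is 46.7 to 48.1. Two-sided power is 67 to 68%, against 65.0%.

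The complete-case figures are therefore lower figures. The loss shrinks but does not vanish, and patients lost before any late visit contribute little to the recovery.

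**The case against.** Four objections have force.

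1. **Most of the gap is not attrition.** A reader might infer that missing data take the trial from 80% to 60–65%. The article does not support that: about 10 points are present at zero loss and come from labelling a one-sided result two-tailed. The two effects must be kept apart. Section 2.11 does allow one-tailed tests for a stated directional hypothesis ("in which case one-tailed tests will be applied"), but its power analysis is declared two-tailed, so this clause does not rescue the 51.

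2. **The text can be over-read.** Section 2.11 speaks of participants, without saying whether they are randomised or evaluable. Only the Primary and Secondary Endpoints section and the Discussion attach 80% to 50 per group; the Abstract, section 2 and the opening of section 3 only set enrolment. The remark on missing data points is a general reason for choosing a model and may mean missed visits. It does not forecast a 12-month loss. It shows only that complete data are not taken for granted.

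3. **Being one patient short per group is trivial.** That is so. The 51 and 50 need reconciling as a contradiction; the difference has no real effect on power.

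4. **The rate is assumed and the planned model softens the loss.** Also true, hence the range and the recovery calculation. Baseline adjustment could help too: 51 per group would suffice two-sided with a baseline-to-outcome correlation of about 0.45, since √(1 − 51/63.77) = 0.447. The article does not invoke this in its calculation.

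A fifth objection, that a journal article may leave attrition to the full protocol or SAP, does not stand. An unstated rate alone would be no finding. Here the number required is printed as equal to the number enrolled, so an allowance held elsewhere would contradict this article.

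**Conclusion.** The point holds with its parts separated. The 80% printed for 50 per group presupposes a 12-month result from all 100 patients and does not follow from the stated two-tailed inputs. With complete data, two-sided power for d = 0.5 is about 70%; this is the larger error. Attrition then removes about 2 to 10 further points two-sided, or 2 to 8 one-sided, over an assumed loss of 5 to 20% with a complete-case t-test, and less if the mixed model can draw on late earlier visits. The attrition sizes depend on the assumed rates and equal loss in both arms. The finding that no allowance was made depends on neither.

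This does not show that the trial must enrol more patients or that its analysis method is wrong. The power claim, and the description of the sample as sufficiently powered, need correcting.

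**What to change.** Keep 100 patients.

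- **Section 2.11:** correct the sample-size sentence so that sidedness and number agree. With two-tailed alpha 0.05, 80% power needs 64 per group; 51 is a one-sided result. Reconcile it with the 50 per group given under Primary and Secondary Endpoints.
- **Primary and Secondary Endpoints, and Discussion:** replace the 80% claim and the statement that the sample is sufficiently powered. Possible wording: *With 50 per group, two-sided power for d = 0.5 is about 70% with complete data, and about 60 to 65% if 10 to 20% lack a 12-month assessment (complete-case lower figure, before covariate adjustment or mixed-model recovery).*
- **State the attrition assumption** and its basis. If recovery through the mixed model or gain from baseline adjustment is to be credited, state the correlations used.

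The cost is text changes in three places, with no extra patients or visits. The downside is that the printed power becomes less favourable.
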